## Abstract

**Background:**

Point-of-care ultrasound is a valuable bedside tool that, with adequate training, can reduce diagnostic uncertainty and improve clinical accuracy. Abdominal pain is a frequent complaint in emergency departments and often requires imaging for appropriate management.

**Objective:**

This study aims to assess the impact of bedside clinical ultrasound performed by family physicians on length of stay, number of basic radiological tests, and need for further diagnostic evaluations in adult patients with abdominal pain.

**Methods:**

This is a pilot quasi-experimental study assessing feasibility and viability, with a nonrandomized control group, to be conducted in the Emergency Department of Hospital Comarcal de Riotinto. Adult patients (≥18 y) presenting with abdominal pain will be included. Both groups will receive standard care. In the intervention group, bedside ultrasound will be performed by trained family physicians; in the control group, ultrasound will be performed by radiologists only if deemed necessary. The primary outcome is the improvement in quality of care, assessed through a reduction in emergency department length of stay, fewer basic radiology tests requested, and diagnostic concordance. Secondary outcomes include the need for additional diagnostic studies and the appropriateness of referrals, evaluated through 1-month follow-up and reconsultation.

**Results:**

The first phase of the project began in 2023 with the validation of the data collection form. Subsequently, the patient satisfaction questionnaire was validated, and the results were published in the journal *Care Primary*. The study has received external funding, and patient recruitment is currently ongoing and expected to be completed in December 2025.

**Conclusions:**

This study aims to demonstrate the clinical and organizational benefits of implementing bedside ultrasound by family physicians in emergency care.

## Introduction

Ultrasound is a diagnostic technique based on the emission and reception of high-frequency waves, so-called ultrasound. It is a patient-friendly technique but requires an interpretation of possible artifacts, as well as progression through a learning curve. Ultrasound in the clinical setting complements physical examination in the same medical procedure, as it is accessible and fast and can be reproduced [1].

The use of ultrasound in emergencies began between 1991 and 1992 by surgeons in the United States, and later in 1996, the acronym FAST (Focused Abdominal Sonography for Trauma) was adopted [2]. From then on, the term POCUS (point-of-care ultrasound) also became commonly used [3].

A review in 2019 showed that POCUS was used for a variety of conditions, although most focused on abdominal and obstetric indications with a good level of diagnostic accuracy [4]. Therefore, it seems appropriate to focus this study on abdominal pain, a common pathology encountered in the emergency department. In fact, a 2010 review indicated that the percentage of nonspecific pain was 24%‐44%, followed by acute appendicitis (15.9%‐28.1%), acute biliary disease (2.9%‐9.7%), and bowel obstruction or diverticulitis in older adults [5].

The pathology related to abdominal pain is highly varied, and training in clinical ultrasound requires a minimal learning curve. Consequently, a number of studies have assessed the training and education of professionals in the detection of biliary tract−related diseases. In this study [6], an acceptable level of agreement was found in the detection of hepatobiliary pathology among junior emergency medicine trainee doctors and radiologists after a short training program. In fact, ultrasound performed by emergency department clinicians affects the diagnostic certainty of abdominal pain in the right hypochondrium, particularly when requesting additional diagnostic studies or in patients with uncertain pathology [7]. The ability of emergency department physicians to diagnose cholelithiasis with bedside ultrasound has also been evaluated [8] and more recently also to rule out cholecystitis [9]. Furthermore, a recent review supports the use of POCUS for gallbladder examination by emergency physicians [10], and another review also suggests that this scan may help in arranging outpatient follow-ups if symptoms have disappeared [11].

In the diagnosis of nephrourological pathology such as renal colic, clinical ultrasound is a good diagnostic tool with a high level of accuracy in detecting urinary tract dilation [12]. These patients may also benefit from an improved level of risk stratification [13]. An observational study has already validated an algorithm for patients with flank pain in the examination and detection of urolithiasis [14]. The use of computed tomography for this pathology has increased, so a review was carried out to compare ultrasound as an alternative and safe test for the patient, which concluded that there is sufficient evidence to determine a more rational algorithm for the management of renal colic [15]. The use of POCUS was also found to be associated with a shorter emergency department stay compared to computed tomography [16].

In the emergency department, the length of stay is determined by many factors, such as the patient’s age, the need for laboratory tests, or referral for consultation, but another factor to be taken into account is the need for ultrasound in abdominal pain [17]. In view of the limited time in the emergency department, ultrasound examination by family doctors is regarded as helping to improve the overall diagnosis and treatment of patients [18]. A recent study from October 2022 also analyzed the effect of POCUS in the initial assessment of patients with acute abdominal pain by evaluating the diagnosis and the decrease in patient waiting time without significant changes in the cost of the service [19].

Many of these patients presenting with abdominal pain at the emergency department require the performance of various complementary tests such as simple radiography. However, the diagnostic efficiency of abdominal radiography in urgent pathologies is not related to the high number of examinations performed as reported in this publication [20]. It is sometimes performed as a routine test despite recommendations to reduce radiation doses to patients and to select pathologies requiring radiography more carefully. This review has already indicated that the use of plain radiography in abdominal pain should be limited to very specific indications [21]. The overuse of these complementary tests leads to unnecessary exposure and increased waiting times in the emergency department. This has been supported by another systematic review [22] where 38 original studies were collected, and the conclusion was that, in most cases, their indiscriminate routine use is not indicated.

Finally, the assessment of the quality of health care is complex and highly subjective as it depends on both the care itself and the patient’s expectations. This analysis of the patient’s experience was carried out using a patient questionnaire, in which the patient’s experience of receiving ultrasound scanning at the point of care was rated positively [23]. However, among the multidimensional models for the assessment of the quality of services provided are the SERVQUAL and SERVPERV questionnaires. The SERVPERF model has been used to assess the perception of quality of care in an emergency department [24], outpatient departments [25], hospital units [26], primary care [27], and even reassessment during the COVID-19 pandemic [28]. The score is calculated by the sum of the scores, and the quality of service is deemed to be as high as the total of the sum of the scores [29]. The SERVPERF model allows the level of quality to be measured by patient assessment.

Accordingly, considering that POCUS can assist professionals in the emergency department to exclude serious causes of abdominal pain−related pathologies, as well as to detect other pathologies that could be followed up at home, this study is proposed to assess the impact of its implementation in a hospital emergency department. Furthermore, the implementation of clinical ultrasound is intended to improve the quality of care and analyze the degree of patient satisfaction.

## Methods

### Study Design and Setting

A quasi-experimental pilot study of feasibility and viability with a control group will be carried out at Hospital Riotinto’s Emergency Department. This center is located in the north of Huelva (Spain) and serves a population of almost 70,000 inhabitants with a high geographical distribution, as some localities are more than 80 km away from the hospital.

This study does not require registration in ClinicalTrials.gov as it does not meet the criteria for a clinical trial according to the International Committee of Medical Journal Editors and US Food and Drug Administration definitions. The project is a quasi-experimental feasibility and implementation study conducted in a real-world clinical setting, with no randomization, no experimental interventions, and no administration of investigational drugs or devices. The study aims to evaluate the impact and utility of point-of-care ultrasound performed by family physicians in emergency departments as part of standard clinical practice. Therefore, it is considered a health services research study rather than a clinical trial, and formal registration is not applicable.

The implementation of bedside clinical ultrasound performed by family physicians in the emergency department is hypothesized to reduce patient length of stay as well as the need for additional diagnostic tests, such as plain radiography or specialist-performed ultrasound, thereby improving the overall quality of patient care. The primary objective is to analyze the impact of this intervention on length of stay, the number of simple radiology tests requested, and the necessity for further examinations by radiodiagnostic specialists.

Specific objectives include determining the length of stay for patients receiving clinical ultrasound by family physicians compared to usual care, quantifying and comparing the number of radiographs and ultrasounds performed, and analyzing patients’ diagnostic and clinical progression over at least 1 month of follow-up. In cases where the process is not resolved, the patient can be monitored for the next 6 months. Additionally, the study aims to evaluate the number and outcomes of specialist-requested ultrasounds in relation to those performed by family physicians, identify factors influencing care quality related to patient health and sociodemographic characteristics, perform diagnostic concordance analyses, and assess patient satisfaction with the service provided.

The sample will consist of patients over the age of 18 years presenting with abdominal pain in the emergency department, who will be assigned to the experimental group (POCUS is performed) or the control group (no clinical ultrasound is performed) consecutively. Patients readmitted for the same pathology will be ruled out. Patients will be invited by the investigators to participate freely, and the recruitment will end when the minimum sample size is reached in each cohort.

The inclusion and exclusion criteria are presented in Textbox 1.

Textbox 1.The inclusion and exclusion criteria.

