**Inclusion criteria**
Patients treated at the Emergency Department of Riotinto Hospital during the study and follow-up periodPatients presenting with acute de novo abdominal pain, defined as a clinical condition causing pain localized by the patient between the thorax and the pelvis. Additionally, patients must not have been admitted for the same condition in the previous 3 months.Age ≥18 yearsPatients with sufficient capacity to provide written informed consentExperimental group: Patients will be attended by physicians from the Emergency Department of Riotinto Hospital and by professionals with demonstrated training in clinical ultrasoundControl group: Patients will be attended by physicians from the Emergency Department of Riotinto Hospital and by professionals without demonstrated training in clinical ultrasound

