**Exclusion criteria**
Patients with readmission due to abdominal painPatients who leave the emergency department before completing carePatients followed in other regional health systems or private health carePregnant womenPatients with morbid obesityPatients with severe mental illnessPatients whose clinical severity prevents obtaining informed consentIntercurrent illness that makes participation impossible

The reasons for study discontinuation are as follows: (1) patient withdrawal, (2) withdrawal of informed consent, (3) death, (4) protocol violation, and (5) intercurrent illness preventing continued participation.

Informed consent will be obtained by the attending physician at the time of patient evaluation, prior to any study-related procedures.

For the sample size calculation, emergency department length of stay was used as the primary variable, as it is the only parameter that has been studied to date (19). A 25% reduction in the mean length of stay is expected in the intervention group compared with the control group. According to the multicenter trial [30], the mean length of stay for patients with nontraumatic abdominal pain in the emergency department was 5.2 (SD 3) hours. Assuming a 25% reduction (1.3 h) in the intervention group, with a 2-sided significance level of 0.05 and a power of 80%, and applying a Student *t*-test for independent samples, a minimum of 84 patients per group is required. Considering an anticipated 15% attrition rate, the total number of participants to be recruited will be 194 patients (97 per group).

There will be no randomization of the sample, as the 2 groups will receive the same care as normal for their pathology; however, in the experimental group, the intervention (clinical ultrasound) will also be carried out to test its effectiveness and assess whether it improves the quality of care. It is important to consider that clinical ultrasound is not a regulated ultrasound, but rather a response to a clinical question; therefore, it is not a complex intervention, and with the usual pressure of the service, it can be performed at any time of the year.

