### Variables

The main outcome variables aligned with the study objectives include the length of stay in the emergency department (measured in minutes), the number and type of radiological tests requested, the performance of bedside ultrasound (POCUS), diagnostic concordance, and the patient’s satisfaction with the care received. Sociodemographic variables such as age, sex, and distance from home, as well as clinical and procedural variables, will also be collected.

A complete list of all study variables, including their measurement units or response categories, is provided in Table 2, grouped into thematic blocks: sociodemographic, clinical, diagnostic, and outcome variables.

**Table 2. T2:** Study protocol variables.

Block and variable		Unit or format	Notes or response options
Sociodemographic			
	Identification code	Alphanumeric	Unique ID per patient
	Gender	Categorical	Male or female or other
	Date of birth	Date (dd/mm/yyyy)	Age will be calculated
	Distance to home	Kilometers	Estimated by postal code
Clinical			
	Health problems	Free text or ICD-10^a^	Comorbidities
	Current medications	Free text	List of active treatments
	Vital signs	Numeric (per parameter)	BP^b^ (mm Hg), HR^c^ (bpm), EVA^d^, temperature (°C), SatO_2_ (%)
	Reason for consultation	Free text	Chief complaint
Care process			
	Attending doctor	Code or initials	Family physician ID
	Date or time of arrival	Time stamp	Format: dd/mm/yyyy hh:mm
	Date or time of discharge	Time stamp	Format: dd/mm/yyyy hh:mm
	Origin	Categorical	Self-referred or primary care or ambulance or other
	POCUS^e^ performed	Binary	Yes or no
	POCUS findings	Free text	Based on clinical protocol
	Other tests requested	Categorical or multiple	Blood tests or ECG^f^ or other
	Radiology test performed	Categorical	X-ray or formal ultrasound or CT^g^ or none
	Interconsultation	Binary	Yes or no; specialty if applicable
Outcome			
	Diagnosis	Free text or ICD-10	Final ED^h^ diagnosis
	Discharge referral	Categorical	Home or hospitalization or specialist or follow-up
	Length of stay	Minutes	Calculated from entry and discharge times
	Satisfaction questionnaire	Likert scale or categorical	1‐5 scale or qualitative responses
	Diagnostic concordance	Binary	Yes or no (based on follow-up or second opinion)

a
*ICD-10: International Classification of Disease, Tenth Revision.*

b BP: blood pressure.

c HR: heart rate.

d EVA: Escala Visual Analógica (VAS: visual analog scale).

e POCUS: point-of-care ultrasound.

f ECG: electrocardiogram.

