## Results

The first phase of the project began in 2023 with the validation of the data collection form. Subsequently, the patient satisfaction questionnaire was validated, and the results were published in the journal Care Primary. The study has received external funding, and patient recruitment is currently ongoing and expected to be completed in December 2025.

The project was initiated in 2023. Between March and July 2023, an initial validation phase of the data collection form was conducted. Preliminary findings were presented as a clinical communication at the 44th semFYC National Congress, held in Barcelona, 14‐16 November 2024. A total of 65 patients were included in this first sample, with a mean age of 56.6 (SD 20.0) years, of whom 53.8% (n=35) were women and 46.2% (n=30) were men. The validation of the data collection form showed that 76.9% (n=50) of the ultrasound examinations were performed as point-of-care clinical ultrasounds (POCUS), whereas only 6.2% (n=4) were formal imaging studies referred to the Radiology Department.

Based on this pilot experience, the study protocol was further developed. Funding was subsequently obtained through the 2024 Call of the Fundación Progreso y Salud (Andalusian Public Health System) under the Research and Innovation Projects category in Primary Care, Regional Hospitals, and High-Resolution Healthcare Centers (grant ID: AP-0561‐2024-C5-F2).

Further work focused on refining the study protocol and validating the patient satisfaction questionnaire was published in [31].

Patient recruitment is currently ongoing and is expected to be completed by December 2025. We anticipate that the implementation of POCUS in patients presenting with abdominal pain in emergency settings will lead to a reduction in length of stay and a decrease in the use of additional diagnostic tests, such as plain radiography or formal radiology−performed ultrasound.

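### Groups are defined once by scan received and once by physician training; the definitions part for unscanned patients of trained physicians, and no rule places them

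*Protocol article*

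**What the plan says.** Study Design and Setting describes the sample as patients "who will be assigned to the experimental group (POCUS is performed) or the control group (no clinical ultrasound is performed) consecutively". Read literally, treatment received sets the group.

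Textbox 1 gives a group-specific inclusion criterion that does not mention the scan. Experimental patients are attended by professionals with demonstrated ultrasound training; control patients are attended by "professionals without demonstrated training in clinical ultrasound".

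Two statements connect these descriptions. The Abstract (Methods) says: "In the intervention group, bedside ultrasound will be performed by trained family physicians". The text after Textbox 1 says that "in the experimental group, the intervention (clinical ultrasound) will also be carried out to test its effectiveness".

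Two others leave room for a trained physician not to scan. The same text says that "clinical ultrasound is not a regulated ultrasound, but rather a response to a clinical question". The Variables section lists performance of POCUS among the main outcome variables, and Table 2 records it as a yes/no item ("POCUS^e^ performed"). Table 2 also holds a code for the attending doctor, but no field for group.

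**The concern.** A trained physician's patient who consents and is then not scanned fails the experimental description in Study Design and Setting. The same patient fails the control criterion in Textbox 1. The article does not say where that patient belongs.

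This is more than loose wording, because one of the two stated rules can bias the result. If only scanned patients count as experimental, group membership depends on a decision taken during the stay whose length is being compared. Anything that influences both the decision to scan and the length of stay then enters the group contrast. Length of stay is the variable on which the study was sized. Group membership also decides when recruitment stops, since it ends once the minimum size is reached in each cohort, and the Results section says recruitment is under way.

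**Working it through.** **Where the definitions agree and part**

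| Patient | By scan received (Study Design and Setting) | By physician training (Textbox 1) |
|---|---|---|
| Trained physician, scanned | Experimental | Experimental |
| Untrained physician, not scanned | Control | Control |
| Trained physician, not scanned | Not experimental | Not eligible as control |

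The third row is empty only if scanning is complete. The article does not treat it as complete: if the scan defined the group, the POCUS item would be constant within each group and could not serve as an outcome.

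**The plan's own figure**

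Inputs from the sample-size paragraph: SD 3 h, difference 1.3 h (25% of 5.2 h), two-sided 5% level, 80% power.

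n per group = 2 × (1.960 + 0.842)² × 3² / 1.3² = 83.6, so 84. The stated 84 is reproduced (an exact t-test solution gives 84.6). It does not depend on the group definition, but it supplies the scale for what follows.

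**Bias if unscanned patients drop out of the experimental group, with no true effect**

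Let M be the mean stay of all patients of trained physicians, assumed equal to that of controls. Let c be the share scanned, and g the hours by which scanned patients stay less for reasons unrelated to POCUS. If S is the mean among the scanned, then M = cS + (1 − c)(S + g), so S = M − (1 − c)g. The apparent benefit is (1 − c) × g.

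The documents give neither c nor g; both are assumptions. The rejection rate uses a standard error of 3 × √(2/84) = 0.463 h.

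| c | g = 0.5 h | g = 2 h | Share of the 1.3 h target | Two-sided rejection rate (nominal 5%) |
|---|---|---|---|---|
| 100% | 0 | 0 | 0 | 5% |
| 90% | 0.05 h | 0.20 h | 4% to 15% | 5.1% to 7.2% |
| 50% | 0.25 h | 1.0 h | 19% to 77% | 8.4% to 57.9% |

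If scanned patients would otherwise stay longer, g is negative and the bias hides a benefit.

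**Cost of grouping by physician**

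If unscanned patients gain nothing, the expected difference becomes 1.3 × c.

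| c | Difference | Power at 84 per group | n per group for 80% |
|---|---|---|---|
| 100% | 1.30 h | 0.802 | 84 |
| 90% | 1.17 h | 0.715 | 104 |
| 50% | 0.65 h | 0.289 | 335 |

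**The case against.** The strongest defence is that the article describes one design from two sides: Textbox 1 says who attends each group, and the parentheses in Study Design and Setting say what each group receives. The Abstract and the text after Textbox 1 both have the scan done in the experimental group. Consent comes before any study procedure, which fits grouping before the scan. This stands to the extent that the definitions are compatible and coincide under complete scanning. It does not supply a rule for when scanning is incomplete.

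The Statistical Analysis section plans regression adjustment for confounders. That helps, but may not remove selection by indication. Handling of non-adherent patients may also be left to an analysis plan that is not shown. The point here is narrower: two group definitions are stated, and they differ.

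A reader might infer more than the documents support:

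- **That unscanned patients of trained physicians would be counted as controls.** This would enlarge the bias, but Textbox 1 bars it, because controls must be attended by professionals without demonstrated training.
- **That about 23% of trained physicians' patients go unscanned.** The Results section reports that 76.9% (n=50), in a form-validation sample of 65, "were performed as point-of-care clinical ultrasounds (POCUS"). The denominator is unclear (examinations or patients), and the sample is not said to consist of trained physicians' patients.
- **That crowding or severity determines who is scanned.** No statement says so. On workload, the article says the scan is feasible under the usual pressure of the service.
- **That the database forces an as-treated split.** The attending-doctor code in Table 2 already allows grouping by physician.
- **That an as-treated contrast answers none of the objectives.** One specific objective does compare patients receiving clinical ultrasound with usual care, although the hypothesis concerns implementation.

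**Conclusion.** The point holds in this form: there are two group definitions that diverge for unscanned patients of trained physicians, no rule places those patients, and one of the two definitions would make the comparison as-treated. The definitions are not incompatible, and the bias is conditional. It needs both incomplete scanning and a difference in underlying stay between scanned and unscanned patients.

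On the assumed ranges, the distortion is small when nearly everyone is scanned and approaches the target effect only when half are unscanned and the gap is 2 h. Because c and g are unknown, the calculation shows how the problem scales and does not estimate its size. The definition should be settled before the data are analysed, and preferably while recruitment continues.

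**What to change.** 1. Define group once, as the ultrasound-training status of the first attending physician, following Textbox 1. Set it before the decision to scan and derive it from the attending-doctor code in Table 2.
2. Analyse all consented, eligible patients in that group, scanned or not.
3. Report POCUS performed as adherence, by group. Keep any scanned-versus-unscanned comparison as a labelled sensitivity analysis.
4. Reword the sentence in Study Design and Setting to match.

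The practical cost is a wording change and one derived variable. There are two statistical costs. First, the effect is diluted to the extent that trained physicians do not scan, with the loss of power shown above, so the observed scanning share should be reported beside the result. Second, grouping by physician leaves confounding by physician: trained and untrained doctors may differ in ways that affect length of stay or test ordering. The article should acknowledge that limitation.
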